### Objectives

#### Main Objective and Primary Outcome Measures

The main objective of this study is to measure the impact of a 12-week intervention using a TR in the home of OAs on their feeling of loneliness and social isolation. To measure the impact of TRs on the feeling of loneliness, we will use the UCLA (version 3) [65]. We will assess social isolation using the Multidimensional Scale of Perceived Social Support (MSPSS), which is a tool for measuring the perception of social support that a person has [66]. We will compare the results obtained in the assessments performed at weeks 0, 6, 12, and 24 to identify the possible decreases in the scores of the different scales at different times of the implementation of the TR at home.

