### Determination of Sample Size

The sample size and power calculation for this study were performed based on 1 of the main outcome measures for this study: the feeling of loneliness, as assessed with the Perceived Loneliness Scale (UCLA; version 3) [65]. From a statistical point of view, we consider that the average score for the UCLA scale, observed for people aged 65 years and over, is 31.51/80 [65]. The higher the score, the greater the perceived loneliness is evaluated. Therefore, our hypothesis aims at a decrease in the average score in the UCLA scale of 3-5 points. If we want to show a decrease of 15% in the average score on the UCLA, between the assessment done at week 0 and week 24 with a power of 0.8 and a risk α of .05, then 60 individuals should be included. A decrease in the UCLA loneliness score of 15% after a 12-week implementation of the TR is clinically relevant.

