### Procedure and Time Schedule

All stages of the experimental phase are illustrated in Figure 3, which describes the different actors involved in each step of the experimental phase, its length, the eventual assessment carried out at that moment, and the respective assessment tools.

During their participation in the protocol, the participants complete 4 assessments (including scales and interviews) as shown in Table 3.

The first evaluation is performed at the time of inclusion at week 0 (ie, approximately 1 week before the implementation of the TR in the volunteers’ homes; Figure 4). A second evaluation (intermediate evaluation) is conducted 6 weeks after the beginning of the experiment at home. A third evaluation (final evaluation) is carried out at the end of the implementation phase (week 12). To conclude the participation in the protocol, the volunteers are invited to take part in a final assessment (follow-up evaluation) at week 24, approximately 12 weeks after the robot has been removed from the participants’ homes. Assessments of participants are conducted face-to-face for the inclusion, and then via the video call functionality of the Cutii robot or by telephone at weeks 6, 12, and 24. Semistructured interviews at week 12 are conducted by a psychologist and recorded using a voice recorder to be transcribed and analyzed.

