### Study Limitations

This study has several limitations. First, we did not consider having a confirmed feeling of loneliness or being socially isolated an inclusion criterion for the recruitment of participants, which could limit the impact of the intervention. However, we would like to emphasize that as shown in the literature [7-10], loneliness and social isolation are frequently observed in this age group. Second, the persons recruited for this study were required to have an internet connection at home. This inclusion criteria may induce a bias because OAs who are already internet users may have a more positive view of digital technologies, such as TRs, and be more familiar with them, than people who do not have internet at home. Third, all the volunteers are recruited in Ile-de-France (ie, Paris and its suburbs). Thus, one cannot exclude the possibility that OAs living in other environments (eg, in rural areas) might show an acceptance of robots different from that of OAs living in more urban areas. Fourth, the experimental group was not compared with a control group because of logistical constraints. Fifth, participants in this protocol tested the robot at home in different contexts and periods of the year (eg, lockdown period linked to COVID-19, summer or winter periods, holiday or working periods). Therefore, one cannot exclude the fact that the use of TRs might be different according to the context when it is tested by OAs. Finally, one could discuss the test-retest reliability of the scales (eg, UCLA, MSPSS, and GDS), considering that the authors administer them once every 6 weeks. For example, the UCLA has a test-retest reliability of 1 year. Therefore, using this tool once every 6 weeks could be a potential limitation of this study.

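### The trial is sized on week 0 versus week 24, two visits without the robot, and the primary-outcome text reads week 24 as a time of implementation

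*Protocol article*

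**What the plan says.** All references are to the protocol article.

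- **Determination of Sample Size.** The target is a "decrease of 15% in the average score on the UCLA, between the assessment done at week 0 and week 24". The error rates and the resulting number follow in the same sentence: "with a power of 0.8 and a risk α of .05, then 60 individuals should be included". The closing sentence then uses a different time point: "A decrease in the UCLA loneliness score of 15% after a 12-week implementation of the TR is clinically relevant". The reference mean and the effect in points are given as "the average score for the UCLA scale, observed for people aged 65 years and over, is 31.51/80" and "our hypothesis aims at a decrease in the average score in the UCLA scale of 3-5 points".
- **Main Objective and Primary Outcome Measures.** Results at weeks 0, 6, 12 and 24 are to be compared "to identify the possible decreases in the scores of the different scales at different times of the implementation of the TR at home".
- **Procedure and Time Schedule.** Week 0 is about one week before installation, and weeks 6 and 12 fall in the implementation phase. Week 24 is a follow-up evaluation, "approximately 12 weeks after the robot has been removed from the participants’ homes". The Abstract also describes weeks 12 to 24 as follow-up after the intervention ends.
- **Quantitative Analysis.** UCLA, MSPSS and GDS go into a one-way ANOVA or a Friedman test over the visits.
- **Study Limitations.** It is acknowledged that "the experimental group was not compared with a control group because of logistical constraints", and that season, holidays and COVID-19 lockdown differ between periods of use.

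**The concern.** The robot is absent at week 0, present at weeks 6 and 12, and absent again at week 24. The sample-size section and the primary-outcome section both treat week 24 as a point where the robot's effect should show as a decrease. That conflicts with the schedule, and the sample-size section also conflicts with its own sentence on clinical relevance.

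The choice of contrast matters because there is no control group and the outcome is self-reported by people who know that they have the robot. Comparing two robot-free visits measures only what remains about 12 weeks after removal. A robot that helps while it is in the home and leaves nothing behind would show no difference on this contrast. A fall in score from time, repeated questioning or study attention that lasts to week 24 would show as a benefit. The article does not say whether persistence or a return toward baseline is expected after removal.

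A smaller point on direction: the primary-outcome section looks for decreases across the scales, but a higher MSPSS score means more perceived support (Standardized Scales), so improvement there is an increase.

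**Working it through.** **Inputs.** From Determination of Sample Size: mean 31.51, decrease 15%, power 0.80, alpha 0.05, n = 60. The Results section gives 56 recruited. The SD, the correlation between visits and the sidedness are not stated.

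**Step 1: the plan's own figure.** Delta = 0.15 × 31.51 = 4.73 points, inside the stated 3 to 5. Without an SD, 60 cannot be reproduced. It can only be inverted for the SD of change.

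- Two-sided, normal approximation: SD = 4.7265 × √60 / (1.960 + 0.842) = 13.07.
- Two-sided paired t test (noncentral t): SD = 12.85, a standardised change of 4.73 / 12.85 = 0.368.
- One-sided, normal: SD = 14.72.
- Read as independent groups, two-sided: SD = 9.24 (60 per group) or 6.53 (30 per group).

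The steps below use 12.85 as an assumption. Conversely, an SD of change of 8, 10, 12, 14 or 16 would need 25, 38, 53, 71 or 92 people (two-sided paired t).

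**Step 2: power of week 0 versus week 24, by the share of the 4.73-point fall still present at week 24.** Two-sided paired t, n = 60, noncentrality = share × 4.7265 × √60 / 12.85.

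| Share kept at week 24 | Power |
|---|---|
| All | 80% |
| Half | 29% |
| A quarter | 11% |
| None | 5% (= alpha) |

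The last row does not depend on the SD: the true difference is zero.

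**Step 3: the omnibus test.** Take a four-visit repeated-measures ANOVA with compound symmetry, so the error variance is 12.85² / 2, about 82.6. Noncentrality = 60 × (sum of squared deviations of the visit means from their average) / 82.6.

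- Sustained (0, −2.36, −4.73, −4.73): sum of squares 15.36, noncentrality 11.15, power 80.0%.
- Reversed (0, −2.36, −4.73, 0): sum of squares 15.36, noncentrality 11.15, power 80.0%.

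The exact tie comes from placing half the effect at week 6. With the full effect already at week 6, the figures are 84% (sustained) and 93% (reversed). In both cases the test rejects for either pattern, and rejection alone does not say which one occurred.

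**Step 4: precision of the two proposed contrasts.** The 95% half-width is t × SD / √n, assuming that SD 12.85 applies to each contrast.

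- n = 60: 2.001 × 12.85 / √60 = 3.32 points.
- n = 56: 2.004 × 12.85 / √56 = 3.44 points.
- Range at n = 60: 2.07 points if the SD is 8 (2.001 × 8 / √60) and 4.13 if it is 16.

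A full 4.73-point rebound from week 12 to week 24 would be detected with 80% power at n = 60 and 77% at n = 56, and a half rebound with 29% at n = 60. The 80% is circular, because the SD was solved to give it. It shows only that the removal contrast is no less precise than the sizing contrast if the SDs agree.

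**The case against.** Several points on the other side are sound.

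- A reader might infer that the weeks after removal are the only untreated comparison in the design. They are not. Week 0 is also robot-free, so week 12 versus week 0 already compares robot present with robot absent. Weeks 12 to 24 are the only untreated follow-up period.
- A reader might infer that the plan would score a return to baseline as failure. The primary-outcome section sets no success rule, and the omnibus test is blind to direction. The consequence holds for the contrast used for sizing, not for the test named in the analysis section.
- The Abstract and the schedule already describe week 24 correctly. Part of the defect is inconsistency within one document.
- The expected mechanism (new contacts, belonging, stronger ties) could outlast the robot, so an interest in week 24 is legitimate.
- Follow-up contrasts after an omnibus test are commonly left to an analysis plan, and none is shown here.

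The last two do not remove the point. An aim of lasting benefit would need to be stated, whereas the article ties clinical relevance to the 12-week implementation. The issue is also not an unnamed contrast: the one contrast that the article does name is fixed on a visit that does not match its own relevance sentence.

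**Conclusion.** The point holds as a conflict with a practical consequence. The sample-size and primary-outcome sections must be reconciled with the schedule, and the sizing contrast does not measure the effect of having the robot. Under full reversal its power is 5% under any SD. The intermediate figures (29% with half the effect kept, 11% with a quarter) and the half-widths of 3.3 and 3.4 points rest on an SD of 12.85, which assumes a two-sided paired t test. Other readings give other values.

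A fall followed by a rebound should not be read as proof of a robot effect. Season or lockdown can shift week 24. Assessment mode may shift too: later assessments use the robot's video call or the telephone, and the robot is gone by week 24. Mode also affects week 12 minus week 0, since inclusion is face-to-face. Such a pattern would be supportive only. Equally, an improvement that persists cannot be separated from carry-over, time trend or repeated testing.

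**What to change.** 1. In Main Objective and Primary Outcome Measures, describe week 24 as post-removal follow-up, and state that improvement is a decrease on UCLA and an increase on MSPSS.
2. In Determination of Sample Size, name week 0 to week 12 as the contrast, in line with the section's own relevance sentence, and state the SD of change and the sidedness assumed.
3. Make week 12 minus week 0 the main paired contrast for UCLA and MSPSS, and pre-state week 24 minus week 12 as secondary, each with a 95% CI.
4. State the reading in advance. Improvement followed by loss after removal supports a robot effect but does not establish it, given season, lockdown and assessment mode. Persistent improvement is reported without attributing it to a lasting robot effect.

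The cost is two named contrasts on data already scheduled in Table 3 and a few sentences of text. The downside is that a sustained improvement at week 24 could not be claimed outright as a lasting effect of the robot.

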#### Secondary Objectives and Secondary Outcome Measures

The secondary objective of this study is to establish recommendations for the implementation of TRs in the homes of the OAs. The goal is therefore to study the use of TRs over 12 weeks using ergonomic and health-related and psychosocial criteria. The ergonomic parameters include an evaluation of the perceived usability of the robot software (System Usability Scale [SUS]) [67] and the acceptance of the robot (ALMERE model) [68]. The psychosocial parameters include an evaluation of depressive states (Geriatric Depression Scale [GDS]) [69] and the psychosocial impact of the robot (Psychosocial Impact of Assistive Devices Scale [PIADS]) [70]. These secondary outcome measures are assessed at weeks 6 and 12 (Table 3).

These assessments will help us determine whether TRs are useful tools to reinforce social contact for OAs living at home. We will identify the most suitable target population (eg, autonomous OAs, dependent OAs) as well as the most suitable framework and environment of use (eg, home, senior residence) for the deployment of TRs. We will also suggest organizational, ethical, and practical recommendations for the implementation and use of TRs by community-dwelling OAs.

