### TRs: A Solution That Has Not Been Thoroughly Studied for Seniors Living at Home

Since the beginning of the COVID-19 health crisis, different stakeholders have shown an increasing interest in innovative remote communication solutions and TRs [25-38]. However, thus far, there is limited available evidence concerning the implementation and usefulness of TRs in a home-dwelling OA population. TRs have so far been studied mainly in controlled settings [39-49], although some studies involving OAs have been conducted in institutional settings (hospital services or senior residences) [50-58] and a few of them at home [59-63]. In particular, studies conducted with OAs at home have highlighted the benefits and issues associated with the use of TRs.

With regard to the benefits of using TRs at home, cognitively healthy users have had a positive experience [60-63]. Participants in the experiments reported good acceptance, usability, perceived usefulness [59], and reliability of the TRs [63]. In the study by Cesta et al [43] the users mentioned good social and functional acceptability of the robot without any loss of interest in its use over time. They considered the mobility, entertainment, and obstacle detection features of the robot to be satisfactory [61]. They mentioned that TRs could be beneficial for physical health, psychological well-being, social contact, and independent living [60]. In the trial carried out by Bakas et al [62], OAs showed an improvement in quality of life and sleep, as well as a decrease in depression following a TR intervention.

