## Methods

### Study Design

The DOMIROB protocol is a nonrandomized, quasi-experimental field trial using a multimethod and multidimensional assessment. The experimental phase of the study took place between September 2020 and February 2023. Volunteer OAs were recruited between September 2020 and August 2022 in Paris, France. This study included 60 OAs who agreed to host and use a TR in their home for a period of 12 weeks.

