The ALMERE model [68] measures OAs’ acceptance toward socially assistive robots. It can be used to predict and understand the use of a system by observing the influences on the intention to use it. The ALMERE model questionnaire is composed of 39 items divided into 13 dimensions: “Anxiety,” “Attitude Towards Technology,” “Facilitating Conditions,” “Intention to Use,” “Perceived Adaptiveness,” “Perceived Enjoyment,” “Perceived Ease of Use,” “Perceived Sociability,” “Perceived Usefulness,” “Social Influence,” “Social Presence,” “Trust,” and “Use.” These dimensions predict the actual intention to use the system. To answer the items, the participants respond using a 5-point Likert scale ranging from “1=strongly disagree” to “5=strongly agree.” Scores of 1 and 2 represent poor satisfaction, 3 denotes fair satisfaction, 4 means good satisfaction, and 5 promotes excellent satisfaction.

The PIADS [70] is a self-report questionnaire designed to assess the effects of an assistive device on functional independence, well-being, and quality of life. Participants respond to 26 items on a 7-point Likert scale ranging from “–3” to “+3.” The final score of –3 represents the strongest negative impact, 0 indicates no perceived impact, and 3 denotes the strongest positive impact.

Measurements performed during the experimental phase of the DOMIROB study are listed in Table 1. The calendar of the assessments is specified in Table 2.

**Table 1 table1:** DOMIROB project protocol measures.

Measurement tools	Dimensions assessed
Mini-Mental State Examination (MMSE) [72]	Global cognitive efficiency
Perceived Loneliness Scale (UCLA) [65]	Subjective feelings of loneliness
Multidimensional Scale of Perceived Social Support (MSPSS) [66]	Perceived social support (social isolation)
Depression: Geriatric Depression Scale (GDS) [69]	Depressive states
Perceived health status: 12-item Short Form Health Survey (SF-12) [73]	Self-assessment of health
System Usability Scale (SUS) [67]	Telepresence robot usability
Acceptance model (ALMERE) [68]	Telepresence robot acceptance
Psychological Impact of the Assisted Device (PIADS) [70]	Psychosocial impact of a device
Sociodemographic data	Age, socioeducational level, and family status

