The use of the MARTA model was chosen because the study conducted by Cesta et al [43] has many similarities with the DOMIROB project. Both studies aimed to evaluate the usability and acceptability of TRs in an ecological setting with an elderly population. The adaptability of the MARTA model allows us to define a protocol that meets our objectives. As our main aim is to measure the impact of TRs on social isolation in OAs living at home, we chose to keep the psychosocial scales of the MARTA model, although not all of them were used in the study by Cesta et al [43]. Further, 2 participants included in this study lived together. Two scales, namely, the Temple Presence Inventory (TPI) [76] and the Positive and Negative Affect Schedule (PANAS) [77], were excluded from the DOMIROB project to reduce the number of assessment tools and to limit fatigue and cognitive overload in OAs during the evaluations. Indeed, the Cesta et al [43] study was carried out over a period of 12 months with only a couple of OAs, whereas the DOMIROB project aims to recruit 60 participants, with each volunteer participating in the study for 6 months during a total experimental period of 18 months.

The DOMIROB project is a truly comprehensive study on the implementation of TRs for OAs living in home, particularly regarding the psychosocial impact of TRs on OAs in home. It is also the first study to include a multidimensional assessment of both psychosocial and ergonomic aspects. This trial will allow the identification of OAs’ profiles for whom the implementation of TRs seems the most relevant. We expect that TR implementation for OAs at home could contribute to limit their social withdrawal. However, it is also conceivable that TRs fail to meet the main aim of the intervention, that they are unsuitable for the users’ homes, or that their use and maintenance require significant help, thus limiting their interest for OAs who cannot regularly benefit from the assistance of a third person.

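### The secondary objectives promise conclusions on setting (home or senior residence) and on autonomous versus dependent users that a home-only sample with no dependency measure cannot supply

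*Protocol article*

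**What the plan says.** The protocol article, under Secondary Objectives and Secondary Outcome Measures, sets the secondary objective as recommendations for using telepresence robots in older adults' homes. It lists the SUS, ALMERE, GDS and PIADS as the measures that serve it. It then states what the assessments will establish: "We will identify the most suitable target population (eg, autonomous OAs, dependent OAs". The same sentence goes on to make a like promise about setting, namely to find the "most suitable framework and environment of use (eg, home, senior residence". Both pairs are given as examples. The Discussion, under Expected Findings, says that the trial will identify user "profiles for whom the implementation of TRs seems the most relevant"; that sentence names neither dependency nor setting.

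On who is studied and where, Study Design says: "This study included 60 OAs who agreed to host and use a TR in their home for a period of 12 weeks". Agreeing to host the robot in the home is also an inclusion criterion.

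**The concern.** To say which of two settings or two populations suits the robot better, the study needs both represented and a variable that tells them apart. The sentence on suitability promises a finding on each, yet the enrolled sample and the listed measures appear to provide neither the second setting nor a way to class people as autonomous or dependent.

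The stake is the secondary objective. Its product is a set of implementation recommendations and, according to the Discussion, a users' guide. A statement there that robots suit homes better than senior residences, or autonomous people better than dependent ones, would look like a trial finding when the trial never made that comparison.

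**Working it through.** No arithmetic applies. The check sets each promise against the sample and the measures.

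**Setting of use**

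1. Groups: one. All 60 planned participants host the robot in their home (Study Design; inclusion criteria), and the limitations section confirms that there is no comparison group.
2. Could a senior residence count as home? The Introduction separates them: it describes earlier studies "conducted in institutional settings (hospital services or senior residences") and sets these apart from studies at home.
3. If some participants did live in a senior-residence flat, could they be identified? Table 1 gives the sociodemographic data as "Age, socioeducational level, and family status". The Measures section spells these out further: living alone or with others, and having children or grandchildren. Housing type is in neither list. The suitability of the dwelling for the robot is an eligibility filter, not a recorded setting.
4. Result: one setting and no variable to divide it, so no difference between settings can be estimated.

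**Autonomous versus dependent**

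The measures in Tables 1 and 3, against what would be needed:

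| Measure | When | Grades the participant's functional dependency? |
|---|---|---|
| MMSE | week 0 | No: global cognition, with scores under 20 excluded |
| SF-12 | week 0 | No: perceived health |
| Sociodemographic data | week 0 | No |
| UCLA, MSPSS, GDS | weeks 0, 6, 12, 24 | No: loneliness, perceived support, depressive state |
| SUS, ALMERE | weeks 6, 12 | No: usability and acceptance of the robot |
| PIADS | weeks 6, 12 | No: effect of the device on independence and well-being |
| Interview | week 12 | No: opinion on eight technology-assessment dimensions |

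The SF-12 and PIADS come closest. The SF-12 is the participant's own view of health. The PIADS is an outcome of using the device, measured after it is installed, so it cannot define who was dependent beforehand. The Introduction's account of which measures were kept from the MARTA model agrees with this list. Excluding people with MMSE under 20 or under guardianship or curatorship probably narrows the dependent range further.

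Result: the listed data do not allow participants to be classed as autonomous or dependent.

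**Interview**

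Table 2 asks about effect on well-being, features, risks, loneliness, cost, ethics, skills needed and reasons not to use the robot. No question asks which population or setting suits it, though answers may touch on either.

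**The case against.** The strongest reply is that the sentence is an aspiration with examples, not a designed comparison. No test or estimand by setting or dependency is stated, and the surrounding text speaks of homes and community-dwelling people. The interviews are meant to feed recommendations, and their framework analysis allows emergent themes, so remarks about suitability need not come from subgroup tests. Much of this stands, and it limits the point in four ways.

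- A reader might infer that nothing can be said about target population. The documents do not support that: cognition, perceived health, depressive state, age and living situation are all collected at week 0 and can describe profiles.
- A reader might infer that the analysis section is deficient because it names no moderator analysis. With a condensed article and no analysis plan at hand, that cannot be held against it.
- A reader might want a power figure for the missing contrast. The article gives no SD of change, and any split would be invented for a variable that is not measured. The point does not need one.
- A reader might take the Discussion to repeat the setting claim. It speaks only of profiles.

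The reply does not rescue the two named examples. Interview opinion from people who used the robot at home is not evidence on which setting is most suitable, and the text promises identification without that qualification. The limitations section mentions internet access and urban recruitment but not this gap.

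**Conclusion.** The point holds for the two conclusions the article names. The setting conclusion fails outright because only one setting is enrolled. The target-population conclusion fails for autonomous versus dependent, but not for every profile. Severity is minor to moderate: what the trial may recommend is affected, while the primary outcome, the named secondary measures and the stated tests are not.

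This rests on Tables 1 and 3 being the full list of measures. Multimedia Appendix 1, which holds the assessment tools, is not shown. If it contained a dependency scale or a housing item, the corresponding part would fall away. An analysis plan alone could not change the conclusion, since it cannot supply data that were not collected.

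**What to change.** In Secondary Objectives and Secondary Outcome Measures:

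1. Remove the home versus senior-residence conclusion, or attribute any statement about other settings to interview opinion only. Restrict the recommendations to home-dwelling older adults.
2. Replace the autonomous/dependent example with a short list of profiles built from week 0 variables already collected, such as MMSE, SF-12 and living alone. Leave baseline UCLA off the list, because its relation to change in UCLA is prone to regression to the mean.
3. Report the profiles descriptively with confidence intervals, separately from the primary ANOVA or Friedman test; the Friedman test has no place for a moderator term. Label them exploratory, because the study is uncontrolled and has about 60 people.

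In Expected Findings, label the statement about profiles exploratory as well.

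The cost is a change of wording and a small descriptive analysis of existing data, with no new collection. The downside is a more modest secondary conclusion.
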